**ABBREVIATIONS**

|         |                                                                                   |
|---------|-----------------------------------------------------------------------------------|
| AE      | ADVERSE EVENT                                                                     |
| ALP     | ALKALINE PHOSPHATASE                                                              |
| ALT     | ALANINE TRANSAMINASE                                                              |
| ANC     | ABSOLUTE NEUTROPHIL COUNT                                                         |
| AR      | ADVERSE REACTION                                                                  |
| AST     | ASPARTATE TRANSAMINASE                                                            |
| CALR    | CALRETICULIN                                                                      |
| CBSB    | CAMBRIDGE BLOOD AND STEM CELL BIOBANK                                             |
| CR      | COMPLETE RESPONSE                                                                 |
| CRF     | CASE REPORT FORM                                                                  |
| CR UK   | CANCER RESEARCH UK                                                                |
| CRCTU   | CANCER RESEARCH UK CLINICAL TRIALS UNIT (UNIVERSITY OF BIRMINGHAM)                |
| CTCAE   | COMMON TERMINOLOGY CRITERIA FOR ADVERSE EVENTS                                    |
| CV      | CURRICULUM VITAE                                                                  |
| DCF     | DATA CLARIFICATION FORM                                                           |
| DNA     | DEOXYRIBOSE NUCLEIC ACID                                                          |
| DSUR    | DEVELOPMENT SAFETY UPDATE REPORT                                                  |
| DVT     | DEEP VEIN THROMBOSIS                                                              |
| ECOG    | EASTERN COOPERATIVE ONCOLOGY GROUP                                                |
| eCRF    | ELECTRONIC CASE REPORT FORM                                                       |
| eGFR    | ESTIMATED GLOMERULAR FILTRATION RATE                                              |
| eRDC    | ELECTRONIC REMOTE DATA CAPTURE                                                    |
| ET      | ESSENTIAL THROMBOCYTHAEMIA                                                        |
| FBC     | FULL BLOOD COUNT                                                                  |
| GCP     | GOOD CLINICAL PRACTICE                                                            |
| GP      | GENERAL PRACTITIONER                                                              |
| HB      | HAEMOGLOBIN                                                                       |
| HC      | HYDROXYCARBAMIDE                                                                  |
| HCT     | HAEMATOCRIT                                                                       |
| ICF     | INFORMED CONSENT FORM                                                             |
| ISF     | INVESTIGATOR SITE FILE                                                            |
| IMP     | INVESTIGATIONAL MEDICINAL PRODUCT                                                 |
| ISRCTN  | INTERNATIONAL STANDARD RANDOMISED CLINICAL TRIAL NUMBER                           |
| IWG     | INTERNATIONAL WORKING GROUP                                                       |
| IWG-MRT | INTERNATIONAL WORKING GROUP – MYELOPROLIFERATIVE NEOPLASMS RESEARCH AND TREATMENT |
| JAK     | JANUS KINASE                                                                      |
| LDH     | LACTATE DEHYDROGENASE                                                             |
| MF      | MYELOFIBROSIS                                                                     |
| ML      | MILLILITRE                                                                        |

---

|       |                                                     |
|-------|-----------------------------------------------------|
| MHRA  | MEDICINES AND HEALTHCARE PRODUCTS REGULATORY AGENCY |
| MPL   | MYELOPROLIFERATIVE LEUKAEMIA                        |
| MPN   | MYELOPROLIFERATIVE NEOPLASMS                        |
| NIHR  | NATIONAL INSTITUTE FOR HEALTH RESEARCH              |
| OD    | ONCE DAILY                                          |
| PE    | PULMONARY EMBOLISM                                  |
| PI    | PRINCIPAL INVESTIGATOR                              |
| PIS   | PATIENT INFORMATION SHEET                           |
| PMF   | PRIMARY MYELOFIBROSIS                               |
| PO    | BY MOUTH (PER OS)                                   |
| PR    | PARTIAL RESPONSE                                    |
| PV    | POLYCYTHAEMIA VERA                                  |

## 1. BACKGROUND AND RATIONALE

### 1.1 Background

The myeloproliferative neoplasms (MPN) comprise several clonal haematological malignancies including polycythemia vera (PV), essential thrombocythemia (ET) and primary myelofibrosis (PMF). MPN results from transformation of a haematopoietic progenitor cell and are characterised by overproduction of mature functional blood cells and have a chronic clinical course. Patients are at increased risk of arterial and venous thrombosis, major haemorrhage and, in the longer term, transformation to myelofibrosis and/or acute leukaemia. It is estimated that approximately 3,000 new patients are diagnosed with MPN per annum in the UK [4].

There are currently no curative options for patients with MPN other than stem cell transplant which is only suitable for a minority of patients. Instead our current therapies are mainly aimed at controlling the abnormal numbers of blood cells and reducing the risk of thrombotic and haemorrhagic events without exposing patients to increased risk of transformation into myelofibrosis or leukaemia [5].

Venesection and low dose aspirin are accepted as the standard of care for initial therapy with the addition of hydroxycarbamide (HC) to reduce the platelet count [6]. Current research in this area is mainly focussed upon JAK inhibition and the use of interferon. These trials are only open to patients with newly diagnosed high risk MPN (MPD RC112 interferon vs hydroxycarbamide) or those who have become resistant or refractory to hydroxycarbamide (MAJIC). None of these studies are targeting reduction of the abnormal disease clone. More recently JAK inhibitor therapy has become an option for some patients. Ruxolitinib is licenced for the treatment of disease-related splenomegaly or symptoms in adult patients with PMF or post ET/PV-MF and has also recently been licensed for the treatment of adult patients with PV who are resistant to or intolerant of hydroxycarbamide. However, access is very limited due to cost, especially in patients with PV and this approach does not offer a cure.

In this trial we are therefore seeking to try to build upon the success of current therapies, which reduce risks of thrombosis and haemorrhage, and find a therapy which moves the treatment target towards a molecular eradication of the disease which is very rarely achieved with current therapies.

The discovery of the JAK2-V617F mutation provided the first genetic marker of the malignant clone in MPN. It is present in >95% of those with PV and approximately 50-60% of ET and PMF patients [7, 8]. JAK2 activation is a consistent pathological finding in MPN, even in those patients without the JAK2-V617F mutation. There is good evidence that JAK2 activation drives much of the platelet and leukocyte activation found in these disorders, and is associated with thrombosis, especially venous events [9]. Furthermore, the presence of the JAK2-V617F mutation is associated with poorer survival in patients with PMF [8]. There is also evidence that a high JAK2-V617F mutant allele burden is associated with features of more advanced disease [10, 11] in particular, it is associated with factors such as thrombosis [12] and myelofibrotic transformation [13] which result in poor outcomes for patients.

More recently, it was also discovered that CALR mutations were present in 25% and 35% of patients with ET and PMF respectively [14]. When looking at patients without JAK2 or MPL mutations, the incidence of CALR mutations is as high as 70- 84% [15]. The impact of a high CALR mutant allele burden has not yet been elucidated.

The potential role of tamoxifen in treating MPN has recently been assessed *in vivo* by the [name] group. These data indicate that accumulation of abnormal blood cells and bone marrow degeneration (caused by MPN) are both blocked in mouse models by treatment with tamoxifen. Tamoxifen mimics the effects of oestrogen and is able to regulate the survival, proliferation and self-renewal of stem cells that give rise to blood cancers. In MPN mouse models, tamoxifen treatment blocked the excessive production of blood cells by restoring normal levels of programmed cell death in mutant blood progenitor cells. The effects of tamoxifen were more pronounced in the mutated cells than in the normal cells, allowing for a reduction in the tumour size [16].

Polymorphisms in the oestrogen receptor-alpha have been suggested to confer susceptibility to develop acute myeloid leukaemia. This gene is also frequently methylated in this disease and its methylation status might predict prognosis. Its re-expression after treatment with hypomethylating agents also correlates with clinical response [17-21]. The results of the correlative science will also be potentially important in assessing which patients might benefit from tamoxifen therapy.

## 1.2 Trial Rationale

### 1.2.1 Justification for patient population

This trial will be open to all patients with MPN who have a measureable disease burden (defined by quantifiable abnormal clone of  $\geq 20\%$  mutated JAK2-V617F, CALR 5bp insertion (exon 9) or CALR 52bp deletion (exon 9)).

The eligibility criteria have also been carefully considered to take into account the well-established safety profile of tamoxifen and the trial is therefore open only to males and post-menopausal women.

Patients with a prior thrombosis will also be excluded as both tamoxifen and MPN are associated with a higher risk of thrombosis. To try and ensure patients have stable blood counts whilst on trial, and again minimise the risk of thrombosis, patients will also be able to continue with existing therapy for their MPN such as hydroxycarbamide, venesection, and aspirin. However, patients will not be able to continue/receive concomitant treatment with therapies that lower the allele burden such as interferon alpha) as this would prevent accurate assessment of the primary outcome. JAK inhibitors, such as ruxolitinib, will be allowed if taken continuously for  $\geq 6$  months prior to registration, as any changes in allele burden are expected to occur early during treatment.

In addition, only patients whose disease is currently well controlled on standard therapies will be eligible which will further minimise the risk of thrombosis.

Another well described side effect of tamoxifen is women experiencing symptoms of premature menopause and uterine changes. This study will therefore only include post-menopausal women.

### 1.2.2 Justification for design

This will be the first trial of tamoxifen in MPN and it is designed to gather preliminary evidence of activity.

A safe dose of tamoxifen is well-established in other malignancies and *in vitro* data indicates that this dose would be effective in this population of patients. A single arm phase II study was selected in order to determine evidence of activity in MPN to further evaluate in a randomised phase 3 setting. An Ahern's design was selected to evaluate activity with stopping criteria to evaluate toxicity given that tamoxifen has not been used in this disease area and in combination with cytoreductive agents.

If this study shows a response (reduction in allele burden of  $\geq 50\%$ ) in  $\geq 10\%$  of patients, it will warrant further investigation in a larger, randomised trial.

In this study, clone size (peripheral blood granulocyte JAK2-V617F, CALR 5bp insertion (exon 9) or CALR 52bp deletion (exon 9) mutant allele burden) reduction by 50% of the baseline value after 24 weeks of treatment will be used as a surrogate endpoint for the effect of tamoxifen on MPN. 50% reduction was chosen as this is an accepted endpoint in the MPN community [22].

This trial will also measure gene expression and methylation and a surrogate of oestrogen receptor signalling, and will correlate the results with disease progression and response to treatment. The goal is to be able to stratify patients according to biomarkers of oestrogen receptor signalling and predictors of clinical response.

### 1.2.3 Choice of treatment

This trial will test tamoxifen; a cheap, widely available drug, with a well-documented safety profile, in a new disease indication. Tamoxifen is a non-steroidal triphenylethylene-based drug which displays a complex spectrum of oestrogen antagonist and oestrogen agonist like pharmaceutical effects in different tissues. Tamoxifen is an established treatment in breast cancer where it acts primarily as an antioestrogen, preventing oestrogen binding to the oestrogen receptor.

Patients will receive 20mg (the most frequently used dose in breast cancer) once daily PO continuously for a minimum of 24 weeks.

This trial will specifically build on the *in vivo* work performed by the [name] group. In this *in vivo* work, low dose tamoxifen was used and a strong response was observed. Therefore, the standard dose of 20mg will be used.

The trial will exploit the novel regulation of blood progenitors by oestrogens which is not currently being investigated elsewhere in MPN and is also fundamentally different from the current strategies, since the primary target of therapy is not the specific mutation/s of the stem cells. The JAK2/CALR mutated cells will be stimulated with a drug that mimics the effects of the natural hormone on the blood progenitor cells but has a much higher potency.

We will also correlate the patient response to treatment with the expression and methylation of oestrogen receptors. This could lead to novel and easier treatments and increase our understanding of the clinical evolution of leukaemias.

## 2. AIMS, OBJECTIVES AND OUTCOME MEASURES

### 2.1 Aims and Objectives

The aim of this trial is to investigate the activity of tamoxifen in reducing the molecular markers of disease burden in MPN. The trial will also look at the safety of tamoxifen in this patient population.

### 2.2 Outcome Measures

#### Primary outcome

- Reduction in the peripheral blood JAK2V617F, CALR 5bp insertion (exon 9) or CALR 52bp deletion (exon 9) mutant allele burden of  $\geq 50\%$  at 24 weeks

#### Secondary outcomes

- Proportion of patients with a reduction in the peripheral blood JAK2-V617F, CALR 5bp insertion (exon 9), or CALR 52bp deletion (exon 9) mutant allele burden of  $\geq 50\%$  at 12 weeks
- Toxicity measured as the number of grade 3 and 4 adverse events reported.
- The number of thrombotic events of any grade reported and validated.
- Haematological response, assessed at weeks 12 and 24, for patients who enter the study in response (CR or PR). Haematological response is defined according to 2009 ELN criteria for ET/PV patients [1] and no evidence of disease progression for MF patients according to IWG-MRT response criteria [2] (for criteria see Appendices 5 & 6)
- Proportion of patients in each response category according to IWG-MRT response criteria [2] for MF patients and 2013 ELN response criteria [3] for ET/PV patients at 24 weeks of treatment
- Proportion of patients showing an improvement in response category at 24 weeks compared to baseline according to 2009 ELN criteria for ET/PV patients [1] and according to IWG-MRT response criteria [2] for MF patients. Patients who are in a higher category at week 24 compared to baseline will be classed a success. Patients who enter the trial in CR and who maintain a CR will also be classed as a success in this outcome

#### 2.2.1 Exploratory outcome measures

- Change in allele burden between weeks 12, 24 and baseline.
- Proportion of patients showing a decrease in requirement for cytoreduction at 24 weeks compared to baseline
- Proportion of patients showing a decrease in allele burden of  $\geq 50\%$  at 36 and 48 weeks compared to baseline
- Duration of reduction in the mutant allele burden, defined as time from first observed reduction of  $\geq 50\%$  until reduction from baseline becomes  $< 25\%$  or patients death.
- Expression (RNAseq), DNA-protein interaction (ChIPSeq) and methylation studies focused on oestrogen receptor signalling in haematopoietic progenitors obtained from peripheral blood and bone marrow before (peripheral blood only) and after tamoxifen treatment

## 3. TRIAL DESIGN

This is a single arm, open label, multicentre, phase II trial of tamoxifen in patients with MPNs.

The aim of the study is to evaluate the activity of tamoxifen in terms of reducing allele burden and the safety of giving tamoxifen in this group of patients. A single stage A'herns design has been chosen to give evidence of activity for the treatment.

All patients will receive a minimum of 24 weeks of treatment with tamoxifen at 20mg od. Patients will be seen at weeks 4, 12, 18 and 24. Mutant allele burden of JAK2-V617F, CALR 5bp insertion (exon 9) and CALR 52bp deletion (exon 9) will be assessed at baseline. Allele burden will be reassessed at 12 weeks and 24 weeks for the mutation(s) identified at baseline. Patients may continue treatment

beyond 24 weeks at the discretion of the treating Investigator. If patients do continue treatment they should be followed up a minimum of 12 weekly and their allele burden reassessed at 36 weeks and 48 weeks as applicable. All patients will be followed up until 28 days after the last dose of tamoxifen treatment.

## 4. ELIGIBILITY

### 4.1 Inclusion Criteria

- Age  $\geq 60$  years (men aged between 50-59 may also be considered following discussion with the Chief Investigator)
- Women must be post-menopausal (defined as amenorrhoeic for at least 12 consecutive months following cessation of all exogenous hormonal treatments)
- Confirmed diagnosis of JAK2-V617F, CALR 5bp insertion (exon 9) or CALR 52bp deletion (exon 9) positive Essential Thrombocythaemia (ET), Polycythaemia Vera (PV) or Myelofibrosis (MF) (primary or secondary) for  $\geq 6$  months
- JAK2-V617F, CALR 5bp insertion (exon 9) or CALR 52bp deletion (exon 9) mutant allele burden  $\geq 20\%$  in peripheral blood granulocyte DNA at study entry (**assessed via central review**)
- WHO performance status 0-2 (see Appendix 1)
- For patients with PV or ET, maintenance of platelet count  $\leq 600 \times 10^9/L$ , WBC  $\leq 25 \times 10^9/L$  and venesection requirements  $\leq 1$  per month for the previous 3 months prior to registration, without introduction of any new therapeutic agents for their MPN for 6 months prior to registration
- For patients with MF, there must not have been any evidence of disease progression\* for the previous 6 months (prior to registration) and no new therapeutic agents for their MPN introduced during this period
- Patients receiving cytoreductive therapy (with the exception of interferon alpha or investigational agents) for their MPN (not solely aspirin or venesection)
- Adequate hepatic function, defined as:
  - bilirubin  $\leq 1.5 \times \text{ULN}$  (patients with elevated bilirubin due to Gilbert's syndrome are eligible)
  - AST/ALT/ALP  $\leq 2.5 \times \text{ULN}$
- Adequate renal function (creatinine clearance  $>30 \text{ mL/min}$ )
- Male patients must agree to use effective contraception during participation in the trial and for 2 months after the last dose of trial treatment
- Patient must be able to give written informed consent

\*Defined by IWG-MRT ELN criteria (Appendix 6). Please note no baseline bone marrow is required to confirm absence of "Leukemic transformation confirmed by a bone marrow blast count of  $\geq 20\%$ ".

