### 7.8 Patient Follow Up

All patients will be followed up until 28 days after the last administration of tamoxifen. This applies if treatment is stopped at 24 weeks, or 28 days after the last treatment if the patient continues beyond 24 weeks. Patients stopping trial treatment early will continue to be followed up for the trial outcomes as per protocol schedule unless the patient specifically withdraws consent.

If patients discontinue study drug prior to 24 weeks, collection of blood samples for central assessment of mutant allele burden should continue to be taken at the protocol specified time points providing the patient received at least 2 months of tamoxifen treatment, and the time point is <3 months from the last date of trial treatment.

Patients continuing trial treatment beyond 24 weeks will have their mutant allele burden reassessed at 36 weeks. Patients continuing trial treatment beyond 36 weeks will have their mutant allele burden reassessed at 48 weeks.

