#### 8.1.2.1 Monitoring pregnancies for potential Serious Adverse Events

It is important to monitor the outcome of pregnancies of patient's partners in order to provide SAE data on congenital anomalies or birth defects.

In the event that a patient's partner becomes pregnant during the SAE reporting period please complete a Pregnancy Notification Form (providing the patient's details) and return to the Trials Office as soon as possible. The patient should be given a Release of Medical Information Form to give to their partner. If the partner is happy to provide information on the outcome of their pregnancy they should sign the Release of Medical Information Form. Once consent has been obtained provide details of the outcome of the pregnancy on a follow-up Pregnancy Notification Form and if necessary also complete an SAE Form.

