### 8.1.3 Reporting period

Details of all AEs (except those listed above) will be documented and reported from the date of commencement of protocol defined treatment until 28 days after the administration of the last treatment. SAEs that are judged to be at least possibly related to tamoxifen must still be reported in an expedited manner irrespective of how long after IMP administration the reaction occurred. Special attention should be paid to women who develop endometrial problems.

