### Serious Adverse Event

Any untoward medical occurrence or effect that at any dose:

- Results in death
- Is life-threatening\*
- Requires hospitalisation\*\* or prolongation of existing inpatients' hospitalisation
- Results in persistent or significant disability or incapacity
- Is a congenital anomaly/birth defect
- Or is otherwise considered medically significant by the Investigator\*\*\*

Comments:

The term severe is often used to describe the intensity (severity) of a specific event. This is not the same as serious, which is based on patients/event outcome or action criteria.

\* Life threatening in the definition of an SAE refers to an event in which the patient was at risk of death at the time of the event; it does not refer to an event that hypothetically might have caused death if it were more severe.

\*\*Hospitalisation is defined as an unplanned, formal inpatient admission, even if the hospitalisation is a precautionary measure for continued observation. Thus hospitalisation for protocol treatment (e.g. line insertion), elective procedures (unless brought forward because of worsening symptoms) or for social reasons (e.g. respite care) are not regarded as an SAE.

\*\*\* Medical judgment should be exercised in deciding whether an AE is serious in other situations.

Important AEs that are not immediately life threatening or do not result in death or hospitalisation but may jeopardise the subject or may require intervention to prevent one of the other outcomes listed in the definition above, should be considered serious.

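### Male contraception runs for 2 months after the last dose, but routine partner-pregnancy notification appears to stop at 28 days, leaving about 31-34 days uncovered

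*Combined protocol and SAP*

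**What the plan says.** Section 4.1, repeated in the synopsis under Main Inclusion and Exclusion Criteria, sets this condition: "Male patients must agree to use effective contraception during participation in the trial and for 2 months after the last dose of trial treatment".

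Section 8.1.2.1 gives the purpose of pregnancy monitoring: "It is important to monitor the outcome of pregnancies of patient's partners in order to provide SAE data on congenital anomalies or birth defects". It then gives the trigger: "In the event that a patient's partner becomes pregnant during the SAE reporting period please complete a Pregnancy Notification Form". The later steps depend on that form. The patient passes a Release of Medical Information Form to the partner, and if the partner agrees, the outcome goes on a follow-up notification form and, if needed, an SAE form.

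Section 8.1.3, headed Reporting period, has AEs documented and reported "from the date of commencement of protocol defined treatment until 28 days after the administration of the last treatment". It then adds an exception without a time limit: "SAEs that are judged to be at least possibly related to tamoxifen must still be reported in an expedited manner irrespective of how long after" dosing the reaction appears.

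Section 7.8 says: "All patients will be followed up until 28 days after the last administration of tamoxifen". Section 3 and the Schedule of Events agree with this.

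Appendix 3 includes this item in its definition of an SAE: "Is a congenital anomaly/birth defect". Pregnancy itself is not in that list.

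**The concern.** The protocol asks men to avoid conception for 2 months after stopping tamoxifen, yet the instruction to notify a partner pregnancy appears to lapse after 28 days. Take a conception in week 6 after the last dose. Contraception is still required then, but the site has no instruction to complete the form that starts outcome follow-up. Section 8.1.2.1 itself calls this follow-up important for data on congenital anomalies. What is at stake is the completeness of one rare kind of safety information. The primary endpoint, the decision rule and the sample size are not involved.

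**Working it through.** The plan gives no figure of its own to reproduce here. The check sets the sections side by side and counts days.

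**Inputs**
- Contraception after the last dose: 2 months (4.1). Assumption: two calendar months, which is 59-62 days, or 56 days if read as 8 weeks.
- End of the stated reporting period: 28 days after the last treatment (8.1.3).
- End of patient follow-up: 28 days after the last dose (7.8).
- Treatment: 24 weeks, 24 × 7 = 168 days (sections 3 and 7.1). Some patients may continue, with reassessment up to 48 weeks, 48 × 7 = 336 days.

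**Step 1: days not covered by routine notification.** Uncovered days = post-dose contraception days − 28.
- 59 − 28 = 31
- 62 − 28 = 34
- Read as 8 weeks: 56 − 28 = 28

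**Step 2: share of the post-dose window.** Share = uncovered days / post-dose contraception days.
- 31/59 = 52.5%
- 34/62 = 54.8%
- Read as 8 weeks: 28/56 = 50.0%

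**Step 3: share of the whole contraception window.** The sentence in 4.1 also covers participation in the trial, when notification does apply. Share = uncovered days / (treatment days + post-dose days).
- 24 weeks: 31/(168 + 59) = 13.7%, and 34/(168 + 62) = 14.8%
- 48 weeks: 31/(336 + 59) = 7.8%, and 34/(336 + 62) = 8.5%

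**Step 4: does the open-ended clause in 8.1.3 close the gap?** It applies to SAEs judged at least possibly related to tamoxifen. A partner pregnancy is not an SAE under Appendix 3, so the clause does not trigger a notification form. A congenital anomaly is an SAE, so a possibly related one remains reportable. For that, the investigator has to become aware of it after scheduled contact with the patient has ended. The clause is therefore a partial backstop.

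**Step 5: effect of aligning the periods.** If notification ran to the end of the contraception period, the uncovered time would fall from 31-34 days to 0.

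**The case against.** The strongest objection is that 28 days is an inference. SAE reporting period is not defined. The 28-day sentence in 8.1.3 is written for AEs, and the sentence after it removes the limit for related SAEs. This stands as a caution about wording: 28 days is the natural reading, since it is the only end date under that heading and coincides with the end of follow-up, but it is not explicit. It does not remove the problem. If 28 days is meant, there is a gap; if something longer is meant, a site cannot tell from the text.

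A reader might go further and infer that over half of the protocol's contraception window is unmonitored. The documents do not support that. Over half is true only of the post-dose part, with months read as calendar months. Over treatment plus 2 months the share is about 14% at 24 weeks of treatment and about 8% at 48 weeks.

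A reader might also infer that the trial has no route to learn of a birth defect, or that a site would be wrong to report a later pregnancy. Neither follows. A possibly related anomaly is reportable without time limit, an SAE form needs no earlier pregnancy form, and 8.1.2.1 does not forbid a late notification. What is missing is a systematic prompt. The SAE Form Completion Guidelines, the Pregnancy Notification Form and the patient information are not available here and may say more.

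Two further points have some force. Section 4.1 gives no reason for the 2 months, so the protocol does not itself say that surveillance must last as long as contraception. And extending the notification period creates no new contact after day 28, so a later pregnancy would still have to be volunteered. The reminder in the fix addresses the second point in part.

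**Conclusion.** The mismatch is real but minor. Contraception is required for 2 months after the last dose, while routine partner-pregnancy notification, on the natural reading of 8.1.2.1 and 8.1.3, stops at 28 days. That leaves about 31-34 of 59-62 post-dose days uncovered, or 28 of 56 if 2 months means 8 weeks.

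The result rests on taking the 28-day limit in 8.1.3 as the SAE reporting period for pregnancies. It supports saying that these days lie outside routine notification. It does not support saying that they are wholly unmonitored, because the clause for related SAEs still applies once an investigator knows of an anomaly.

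Events should be very rare: the trial plans 42 patients of both sexes, and men must be at least 60, or 50-59 after discussion with the Chief Investigator. No efficacy result, decision rule or sample size is affected. The point concerns only whether the reporting periods agree; it takes no position on how long contraception should last.

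**What to change.** Reconcile 4.1, 8.1.2.1 and 8.1.3. In 8.1.2.1, replace the undefined SAE reporting period with a stated pregnancy-notification period, from the start of trial treatment to the end of the contraception period in 4.1. Defining it by reference to 4.1 keeps the two aligned if that criterion is ever amended.

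At the existing 28-day visit, remind male patients to tell the site of any partner pregnancy up to that date.

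The cost is one sentence in the protocol and a reminder at a visit that already takes place. No extra visit, sample or analysis is needed. The downside is an occasional late form, and pregnancies after day 28 will still reach the trial only if the patient reports them.
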